**Fig. 1 Fig1:**
[figure not shown]
Participant Timeline

The outcomes are measured with questionnaires, audiotapes, and short daily phone calls. Completing the questionnaires (including those measuring moderator variables) takes 30 to 45 min per measurement occasion, making the audiotapes takes about 30 min per measurement occasion (i.e., two recordings of 15 min each), and making the phone calls takes two to three minutes each. Furthermore, parents in the behavioral parent training arm fill out the ECBI-I questionnaire at the beginning of and two weeks after each booster session, which takes a couple of minutes.

### Demographic information and clinical characteristics

Parents will provide information on children’s age and gender, on their own and children’s ethnicity, educational background, and household composition, and on children’s previous and ongoing pharmacological and non-pharmacological treatments, medical conditions, and clinical diagnoses (e.g., ADHD, oppositional defiant disorder [ODD], conduct disorder [CD]).

### Outcomes

#### Primary outcome

##### Individually determined daily ratings of behavioral difficulties

The primary outcome is the mean severity of parents’ daily ratings of four selected target behaviors in specific home situations. On the adapted version of the list of target behaviors [33, 36], parents indicate whether the 29 behaviors occur daily (*yes/no*). For the behaviors scored as yes, parents rate the severity on a 5-point Likert scale ranging from 1 (*not severe*) to 5 (*extremely severe*). Behaviors scored as no are coded 0. With a researcher, parents choose four daily occurring target behaviors from this list that they prefer to work on in the training. Parents also indicate in which situation these behaviors occur, using the situations that are included in the Home Situation Questionnaire [37].

For each measurement occasion, during preferably five but at least four consecutive weekdays, short daily phone calls with parents are made to evaluate whether the four selected target behaviors occurred in the past 24 h in the selected situation (*yes/no*). Items scored as no are rated 0 and items scored as yes are rated on a 5-point Likert scale ranging from 1 (*not severe*) to 5 (*extremely severe*). This outcome is measured at all timepoints (T0-T3). For each timepoint, the average score of all four behaviors on all weekdays is used as outcome measure.

#### Secondary outcomes

##### Parent-reported behavioral difficulties

Children's behavioral difficulties are assessed with the Intensity scale of the Eyberg Child Behavior Inventory (ECBI-I) [48]. The Intensity scale consists of 36-items for parents of children aged 2 to 16 and measures the frequency of specific problem behavior on a 7-point Likert scale from 1 (*never*) to 7 (*always*). The convergent and divergent validity and the reliability of the ECBI-I are well established [49]. This outcome is measured at all timepoints, and at the beginning of and two weeks after each booster session for parents who receive the brief behavioral parent training.

##### Child well-being

Child well-being is assessed with the Health-Related Quality of Life Questionnaire (KINDL-R) [50]. Parents rate their children's quality of life on 20 items regarding emotional well-being, self-esteem, family functioning, social contacts, and school, of which the total score will be used. Parents rate the items on a Likert scale ranging from 1 (*never*) to 5 (*all the time*). The KINDL-R has revealed sufficient internal consistency (α = 0.82) [51]. This outcome is measured at all timepoints.

##### Parenting behaviors

Parenting behaviors are assessed with the Alabama Parenting Questionnaire (APQ; [52]). The APQ is a 42-item parent-report measure assessing five categories of parenting practices (involvement, positive parenting, poor monitoring/supervision, inconsistent discipline, and corporal punishment), of which the total score will be used. Parents rate their parenting on a 5-point scale ranging from 1 (*never*) to 5 (*always*), with higher scores representing higher levels of the particular parenting category. The reliability and validity of the APQ are well established [52]. This outcome is measured at all timepoints.

##### Observed parent and child behaviors

To include an observational measurement of parent and child behaviors, parents are asked to audio record their mealtime routines for at least 15 min on two different weekdays. Mealtimes are notoriously busy times in family lives and thus well suited as a setting for an ecologically valid measure. The recordings of mealtime routines are a masked measure (i.e., assessors are not aware of the intervention condition), based on the method that was used by Herbert et al. [53]. Using the recordings, the following behaviors will be scored with a global coding system: parental behavior (both supportive and non-supportive parenting), child misbehavior, and emotional talk. A subsample of recordings will be double coded until sufficient interrater reliability is established. This outcome is measured at all timepoints except T2, to minimize the burden for families.

##### Parenting stress

Parenting stress is assessed with the Parental Stress Scale (PSS; [54]). The PSS is an 18-item parent report scale that measures positive (e.g., emotional benefits) and negative (e.g., restrictions) aspects of parenting, of which the total score will be used. Parents have to agree or disagree with statements concerning parenting on a 5-point scale ranging from 1 (*strongly disagree*) to 5 (*strongly agree*). The adequate reliability (α = 0.83) and validity of the PSS have been demonstrated [54]. This outcome is measured at all timepoints.

##### Parenting self-efficacy

Parenting self-efficacy is measured with the subscale Efficacy of the Parenting Sense of Competence Scale (PSOC; [55]). On the eight items of this subscale, parents rate their capability level and problem-solving ability regarding their parental role on a 6-point scale, ranging from 1 (*strongly disagree*) to 6 (*strongly agree*). The internal consistency (α = 0.76) of the subscale Efficacy has been established [55]. This outcome is measured at all timepoints.

##### Quality of the parent–child relationship

The quality of the parent–child relationship is measured with the parent version of the Parent–Child Interaction Questionnaire-Revised (PACHIQ-R; [56]). On 21 items, parents rate their relationship with their child on a 5-point scale, ranging from 1 (*strongly disagree*) to 5 (*strongly agree*), of which the total score will be used. The PACHIQ-R has been demonstrated to have high internal consistency (ranging between α = 0.79 and α = 0.93) [56]. This outcome is measured at all timepoints.

##### Utilities

Utilities, also called preferred health states, are assessed using quality-adjusted life years (QALYs). QALYs range between 0 and 1, where 0 represents death and 1 perfect health. QALYs are calculated based on the EuroQol-5D-5L (EQ-5D) questionnaire [57, 58], which parents fill out about their child. The EuroQol-5D-5L measures the child’s health with five items (mobility, self-care, daily activities, pain, and anxiety/depression) on 5-level categorical scales. EQ-5D responses will be transferred into QALYs based on the Dutch EQ-5D-5L tariff for adults [59], as a tariff for Dutch children is not yet available. The content and face validity of the EuroQol-5D-5L are well established [58]. This outcome is measured at T0 and T3.

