### Procedure

Parents in the brief behavioral parent training arm receive three sessions of behavioral parent training. The first two sessions take 120 min each and are planned one or two weeks apart. The third session takes 60 min and is planned one week after the second session. To take parents’ and therapists’ availability into account, some flexibility in planning is allowed as long as all three sessions are planned within six weeks with at least one week between two consecutive sessions. After the third session, parents wishing to receive additional support can receive CAU and/or booster sessions. The booster sessions take 60 min each and can be provided maximally once every four weeks up to one year after the last session of the brief behavioral parent training program. Booster sessions can be suggested by the therapist who provided the brief behavioral parent training or by other involved clinicians, or requested by parents themselves.

The trial contains four measurement occasions, see Fig. 1 for the participant timeline. T0 takes place after parents provide consent and are found eligible for participation, before randomization. The first posttreatment measurement (T1) takes place one week after the third session for parents in the brief behavioral parent training arm and eight weeks after T0 for parents in the CAU arm. The second posttreatment measurement (T2) takes place six months after T1 and the third posttreatment measurement (T3) takes place twelve months after T1. Participation in the trial therefore takes approximately 14 months in total. The care families receive at the child mental healthcare center may terminate sooner if they do not need or want care anymore.

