### Statistical analysis

Data will be analyzed on an intention-to-treat basis. To examine the effects of the intervention on the primary and secondary outcomes, we will conduct multilevel analyses (mixed modeling), taking missing data into account [75]. Depending on the fit of the models, up to four hierarchical levels will be distinguished: outcomes (level 1), nested within children (level 2), nested within therapists (level 3), nested within healthcare centers (level 4). Random intercepts at the subject level, therapist level and healthcare center level will be included only if the Likelihood Ratio Test shows a significant improvement of the model fit. Time will be included as short-term (T1) and longer-term (T2, T3) within-subjects factors and condition (brief parent training vs. CAU) as between-subjects factor. The interaction between time and condition will be examined to interpret changes over time between conditions. To examine whether the candidate moderator variables moderate the intervention effects, these variables will also be added as interaction effects to the multilevel analyses.

To assess the cost-effectiveness of the brief behavioral parent training compared to CAU, we will calculate the Incremental Cost Effectiveness Ratio (ICER) from a societal perspective. We will perform both a cost-utility analysis (based on QALYs) and cost-effectiveness analyses (based on the daily ratings of behavioral difficulties and based on ECBI-I scores). An ICER is calculated by dividing the difference in the total costs by the difference in the total effect (either QALYs or the daily ratings of behavioral difficulties and ECBI-I scores, respectively). In these analyses, the costs of healthcare will be used and interpolated to the previous 12 months. We will compare each ICER based on relevant willingness to pay thresholds. Bootstrapping will be used to calculate the reliability of our estimates.

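### The Utilities section equates an EQ-5D tariff score with a QALY, so the cost-utility ratio as written is cost per utility point and not comparable with a per-QALY threshold

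*Protocol article*

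**What the plan says.** In the protocol article, the Utilities section opens with "Utilities, also called preferred health states, are assessed using quality-adjusted life years (QALYs". It then says "QALYs range between 0 and 1, where 0 represents death and 1 perfect health" and gives the conversion: "EQ-5D responses will be transferred into QALYs based on the Dutch EQ-5D-5L tariff for adults". On timing it says "This outcome is measured at T0 and T3".

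The Statistical analysis section plans a cost-utility analysis on these QALYs: "An ICER is calculated by dividing the difference in the total costs by the difference in the total effect". For the numerator, "the costs of healthcare will be used and interpolated to the previous 12 months". The decision rule is "We will compare each ICER based on relevant willingness to pay thresholds"; no threshold value is given.

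Neither section mentions weighting by time or an area under a curve, and neither says how the T0 and T3 values are combined into an effect per child.

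**The concern.** A tariff maps a questionnaire answer to a utility for the moment at which it was given. It contains no time. A QALY is that utility multiplied by the years spent in it. The Utilities section reverses the relation: it measures utilities by way of QALYs, gives the QALY the death-to-perfect-health anchors of a utility, and lets the tariff alone produce it. It also treats the QALY as something that can be read off at a visit, although a QALY accrues over an interval.

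This goes beyond a step left for an analysis plan, because the article gives a conversion and that conversion has the wrong unit. What is at stake is the cost-utility part of the second objective. Thresholds for such an analysis are amounts per QALY, and a ratio per utility point cannot be read against them, however good the cost data are.

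**Working it through.** **Inputs from the document.** T1 in the care-as-usual arm is "eight weeks after T0 for parents in the CAU arm" (Procedure), and T3 follows T1 by 12 months. Utility is observed at T0 and T3 only (Utilities). Costs are put on 12 months (Statistical analysis).

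**Inputs not in the document, assumed for illustration.** Arms equal at T0; utility difference d at T3 of 0.02 to 0.10; extra cost of the programme 1,000.

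**Check of the horizon.** The article states no QALY gain or ratio to reproduce. The length of participation can be checked: 56 days + 365.25 days = 421.25 days, or 421.25/365.25 = 1.153 years = 13.84 months. This agrees with the roughly 14 months given in Procedure.

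**Unit.** QALY difference = area under the curve of (utility in one arm minus utility in the other) over time in years. The text supplies only tariff scores, so with arms equal at T0 the denominator read literally is d, in utility points.

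**Area for different paths of the difference.** By the trapezoid rule, with T1 at 0.153, T2 at 0.653 and T3 at 1.153 years:

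Area = 0.153 × (0 + d1)/2 + 0.5 × (d1 + d2)/2 + 0.5 × (d2 + d)/2

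where d1 and d2 are the differences at T1 and T2. The last column is d divided by the area, that is, the correct ratio as a multiple of the ratio as written.

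| Assumed path | QALY difference | Correct ÷ as written |
|---|---|---|
| Linear from 0, over exactly 12 months | 1/2 × d = 0.50d | 2.0 |
| Linear from 0, T0 to T3 | 1.153/2 × d = 0.577d | 1.73 |
| Reached by T1, sustained (d, d, d) | 0.077d + d = 1.077d | 0.93 |
| Fading (2d, 1.5d, d) | 0.153d + 0.875d + 0.625d = 1.653d | 0.60 |
| Fading (3d, 2d, d) | 0.230d + 1.25d + 0.75d = 2.230d | 0.45 |
| Late only (0, 0, d) | 0.25d | 4.0 |

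If the 12-month window is taken as T1 to T3, the linear path stands at 0.153/1.153 = 0.133d at T1. The area is (0.133 + 1)/2 × d = 0.566d and the multiple is 1/0.566 = 1.77, inside the range of the first two rows.

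**Example.** With extra cost 1,000 and d = 0.05:

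- As written: 1,000/0.05 = 20,000 per utility point.
- Linear: 1,000/(0.05 × 0.577) = about 34,700 per QALY over T0 to T3, or 1,000/(0.05 × 0.50) = 40,000 over 12 months.
- Sustained from T1: 1,000/(0.05 × 1.077) = about 18,600, which is 7% below 20,000.
- First fading path: 1,000/(0.05 × 1.653) = about 12,100.

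With d = 0.02 the written, linear T0-to-T3 and linear 12-month figures are 50,000, about 86,700 and 100,000. With d = 0.10 they are 10,000, about 17,300 and 20,000. The multiples do not depend on d or on the cost.

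**The case against.** The strongest reply is that the article is loose in its terms but does not prescribe a wrong calculation. It nowhere says that the T3 tariff score is the denominator, it does not exclude time-weighting, and the construction of QALYs is commonly left to a fuller plan. Part of this stands: d as the denominator is a literal reading, and other combinations are possible. Averaging the T0 and T3 scores would give 0.5d, numerically the same as the trapezoid over exactly 12 months. It does not remove the point, because the article defines the QALY as a tariff score, and a fuller plan that time-weights would contradict it.

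Three stronger readings might be inferred, and the document does not support them:

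- **That the ratio will look far too favourable.** The factor of 1.7 to 2 needs an assumed linear path. The sessions are completed within weeks, and the Background reports sustained, fading and delayed effects in earlier research. An early or fading effect is as compatible with the text, and the error then runs the other way. The factor of 4 needs an effect that appears only after T2.
- **That the cost-utility conclusion will be wrong.** Rescaling by a positive factor keeps the sign of the effect. If the programme is both better and cheaper, as Objectives and hypotheses would suggest, it dominates on either scale. If it were cheaper but less effective, an inflated effect difference would count against it. No threshold is given, so no changed decision can be shown.
- **That the 0-to-1 range is disproved by 1.15 QALYs.** That maximum belongs to the T0-to-T3 horizon. Over exactly 12 months, perfect health gives 1 QALY and the range is numerically compatible, although it still lacks a time unit.

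**Conclusion.** The point holds as an error of definition and unit. Followed as written, the cost-utility ratio is cost per utility point and is not comparable with a per-QALY threshold, whatever the path of the effect.

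Its numerical size is conditional. With arms equal at T0 and linear change, the ratio as written is too low by a factor of about 1.7 to 2. With an effect reached by T1 and sustained, the correct ratio is about 7% lower than the one written. With the two fading paths it is 0.60 or 0.45 of the one written. Two utility measurements cannot tell these apart, so neither the direction of the error nor a change of decision can be claimed from the document. These directions assume that the programme costs more and does better.

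The primary outcome, the other clinical analyses and the two cost-effectiveness analyses on daily ratings and on ECBI-I scores are not affected.

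**What to change.** In the Utilities section, call the tariff score a utility and remove the sentence that gives QALYs a range from death to perfect health. Define QALYs per child as the time-weighted area under the utility curve, in years, over one stated horizon.

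That horizon should be the same in both arms and match the 12-month cost window in the Statistical analysis section. Running QALYs over the full 1.153 years from T0 to T3 would set nearly 14 months of effect against 12 months of cost. Because T1 is timed differently in the two arms, it could also credit the arm with the longer interval with extra QALYs. If the window is the 12 months ending at T3, the utility at its start has to be read from the interpolated line, and the text should say so.

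In the Statistical analysis section, adjust the arm difference in QALYs for T0 utility, use that difference in the ratio, and state the linear-interpolation assumption beside the result.

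The cost is a few sentences and a little more analysis work, with no new data or visits. The downside is that, under linear interpolation, a programme that costs more and does better will show a less favourable ratio than the present wording gives.

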##### Use of healthcare

Use of mental healthcare within the organization where the child is treated is measured by drawing up an inventory (based on patient records) of the type of care (brief behavioral parent training, booster sessions, CAU) that is used and the duration (in minutes) of this care between T0 and T3 in both arms. The broader use of healthcare within and outside the mental healthcare centers is assessed with the *Vragenlijst Intensieve Jeugdzorg*, a Dutch questionnaire on intensive youth care [60]. This questionnaire assesses the use of a wide variety of healthcare (e.g., contact with general practitioner or medical professionals, use of social services or (alternative) medicines), along with the child’s use of education, contact with judicial authorities, and losses in the productivity of parents. Parents complete this questionnaire about the use and intensity of healthcare of both the child and themselves in the past three months. This outcome is measured at T0 and T3. Both measures of healthcare use (i.e., inventory of care and questionnaire) will be combined to obtain a complete image of all used care.

##### Costs of healthcare

Healthcare costs are estimated from a societal perspective [5]. Costs of mental healthcare are estimated by multiplying the used care by the reference prices provided in the Cost Manual of the Dutch National Health Care Institute. Costs of medication are estimated by using prices provided by the Dutch National Health Care Institute [61]. Costs in other sectors (e.g., education, justice) are estimated by using reference prices provided in the Manual Intersectoral Costs and Benefits [62]. All costs are estimated after families’ participation in the study, when their healthcare use is fully measured.

#### Candidate moderators

In addition to the general demographic and clinical characteristics and some baseline characteristics such as the severity of behavioral problems, the following variables are included to explore whether they moderate the short- (T1) and longer-term (T2, T3) intervention effects: parental attachment as measured with the 12-item version of the Revised Experiences in Close Relationship questionnaire (ECR-R; [63, 64]),parental psychopathology as measured with the 25 items of the Strengths and Difficulties Questionnaire (SDQ) for adults [65], parental reward responsivity as measured with the 8-item Reward Responsiveness (RR) questionnaire [66], and child reward responsivity and punishment sensitivity as measured with the Punishment Sensitivity and Reward Responsivity subscales (combined 22 items) of the Sensitivity to Punishment and Sensitivity to Reward Questionnaire for Children (SPSRQ-C; [67]). All candidate moderators are measured at T0 only and reported by parents.

#### Parent and therapist satisfaction

##### Parents’ satisfaction with the brief behavioral parent training

Satisfaction with the brief behavioral parent training of parents who received the intervention are measured in two ways. First, parents are asked to fill out a self-developed satisfaction questionnaire, which is based on questions of the Parent Satisfaction Questionnaire [68], the Therapy Attitude Inventory [69], and the satisfaction questionnaire that was used in Breider et al. [70]. Parents who received the brief behavioral parent training answer 13 questions about their satisfaction with the brief behavioral parent training at T1 and three questions about their satisfaction with the booster sessions (if used) at T3 on a 5-point scale ranging from 1 (*strongly disagree*) to 5 (*strongly agree*). Parents also grade the brief behavioral parent training generally between 1 (*very bad*) and 10 (*excellent*). Second, one or multiple focus group(s) will be organized with a small number of parents. In the focus group(s), the new program will be qualitatively evaluated and information about feasibility and barriers and facilitators for the implementation of the training in clinical settings will be gathered. The focus group(s) will be held after the inclusion of parents is finished, which is anticipated to be at the beginning of 2025.

##### Therapists’ satisfaction with the brief behavioral parent training

Therapists' satisfaction and opinion about the intervention are measured in two ways. First, therapists will be asked to fill in a self-developed satisfaction questionnaire, which is based on questions of the Parent Satisfaction Questionnaire [68], the Therapy Attitude Inventory [69], and the satisfaction questionnaire that was used in Breider et al. [70]. Therapists have to answer seven questions on a 5-point scale ranging from 1 (*strongly disagree*) to 5 (*strongly agree*) and give the brief behavioral parent training a general grade between 1 (*very bad*) and 10 (*excellent*). Second, one or multiple focus group(s) will be organized with a selection of therapists from different healthcare centers who provided the brief parent training and range in years of work experience and to how many families they have provided the brief behavioral parent training. In the focus group(s), important barriers and facilitators for the implementation of the program will be identified. Both outcomes will be measured after the trial is finished, which is anticipated to be at the beginning of 2026.

